### Blinding

As this study involves exercise intervention, it is impossible to blind the exercise coaches and participants. To minimize ascertainment bias, the assessors and statistics analyzers will be blinded by two types of blind codes. The allocation result (the Yijinjing exercise group or the routine rehabilitation group) will be showed by using the alphabet “A” or “B” as the first blind code, and then the second blind code represents the real allocation meaning. At the end of the data analysis, the independent research assistant will match the group code “A” or “B” of participants with the real meaning of the group “A” or “B.”

### Intervention

#### Yijinjing exercise group

The participants will receive routine treatment, as well as receive the Yijinjing exercise. The Yijinjing exercise consists of a 12-week Yijinjing practice with 40 min a session, 3 sessions a week. The session has three parts: the warm-up for 5 min, the Yijinjing exercise for 30 min, and the muscle stretching for 5 min. The whole set of the Yijinjing exercise consists of 12 postures (see Fig. 3). Each posture will be demonstrated to the participants, and the Yijinjing exercise is supervised throughout the trial. The same researcher will instruct all participants who will be required to maintain their normal lifestyle, and the postures will be individualized based on their ability.

**Fig. 3 Fig3:**
[figure not shown]
Twelve postures of Yijinjing exercise. The teacher in the image is [name], who has agreed to the publication of the images

#### Routine treatment group

With 5 PTs, 5 OTs, and 5 acupuncture physicians providing treatment, the routine treatment group will receive regular rehabilitation services delivered by certified physical therapists, certified occupational therapists, and certified acupuncture physicians, which will be carried out following the inpatient treatment plan. Besides, all participating therapists will be uniformly trained before starting this research to standardize the treatment further. The rehabilitation services include physical therapy (exercise therapy, balance training, joint mobilization), occupational therapy (homework training, hand training, cognitive dysfunction training), acupuncture therapy, and health education.

#### Concurrent treatment

Other cognitive therapies will be not permitted in both two groups, including cognitive stimulation therapy, cognitive-behavioral therapy, and memantine drugs. There are no arrangements for ancillary or post-trial care.

### Outcome measures

#### Primary outcome measures

Montreal Cognitive Assessment-Beijing Version (MoCA): MoCA, a screening tool to assess mild cognitive impairments with a total score of 0–30 [15], will be administered to evaluate global cognition. The assessment domains include visuospatial or executive function, naming, memory, attention, language, abstraction, and delayed memory and orientation [16]. To avoid the learning effect, we will use MoCA 7.1 and MoCA 7.2 for alternate testing.

#### Secondary outcome measures

Trail Making Test-A (TMT-A): Studies have shown that executive function is a powerful predictor of disability recovery in patients with acute stroke [17]. Therefore, executive function will be assessed separately using the Trail Making Test-A (TMT-A) [18]. TMT-A is a valid index to assess executive function [19, 20]. The test requires the participants to connect number 1 to 25 sequentially on a piece of paper. The completion time and error numbers will be recorded. Longer time indicates severer cognitive impairment.Chinese vision of the Auditory Verbal Learning Test (AVLT): AVLT will be used to measure memory function, including immediate recall, delayed recall, and recognition. In the immediate recall subtest, participants will be required to repeat after 15 common words immediately after the administrator say the word three times. In the delayed recall subtest, participants will be required to recall the 15 words after 30 min. In the recognition, the tester will be given another 15 unrelated words and 15 words of Part A and required to recognize the original words. Evidence showed that AVLT is a valid assessment tool and more sensitive than the Mini-Mental State Examination (MMSE) and MoCA in assessing memory function [21].Rey Complex Figure Test (RCFT):RCFT will be used to assess visuospatial constructional functions [22]. It uses geometrical figures, including repeated squares, rectangles, triangles, and various other shapes. Participants are asked to copy and then reproduce from memory after 30 min. The total score is 36 points, and the test scores reflect the patients’ visual-construction and motor planning skills.Pittsburgh Sleep Quality Index (PSQI): PSQI will assess the participants’ sleep quality, which consists of 18 self-rated items including 7 domains: subjective sleep quality, sleep latency, sleep duration, habitual sleep efficiency, sleep disturbance, use of sleep medication, and daytime dysfunction over the last month [23]. The participants will answer questions using a 3-point Likert scale. The higher their scores reach, the worse the sleep quality is [24, 25].ODONATE 3D: The ODONATE 3D motion capture, a gait analysis system of Shanghai Maiwo medical technology co. LTD, will assess gait parameters, including the space-time, balance, kinematic, and dynamic parameters. Specific operations are as follows: (1) select the appropriate scene and debug the equipment, (2) set the walking area and guide the patients to complete the walking cycle, (3) the artificial intelligence system captures information, and (4) analyze the captured information.Fugl-Meyer Assessment Scale (FMA)-Motor Function Subtest: FMA Motor Function Subtest will assess motor function. FMA is a three-level cumulative scale to evaluate stroke patients’ sensorimotor recovery with hemiplegia [26]. In this study, the Motor Function Subtest will be used with a total point of 100 (66 points of the upper limb, 34 points of the lower limb). Evidence has shown that FMA is sensitive and reliable [27, 28].Berg Balance Scale (BBS): BBS will assess the balance function by 14 tasks as the quantitative assessment of static and dynamic balance function [29]. BBS is a reliable tool to measure balance function of older adults and disabled people [30, 31], and it can also be used as a risk predictor for accidental falls in stroke patients [32].Modified Barthel Index (MBI): MBL consists of 10 items with 100 points in total [33] and will assess ADL. A higher score indicates a better ability to live independently. Its validity and reliability in evaluation for stroke patients have been reported [34].Short Form 36 Health Survey Questionnaire (SF-36): SF-36, a self-rated assessment, will assess comprehensive self-perceived QOL, such as general health conditions and physical and mental health [35]. Studies have shown high response rates from older stroke patients [36].

### Adherence

All participants in both intervention and control group will be required to log in their activity duration and intensity in a timesheet. The participant will rate the duration and intensity of their activity based on self-perception throughout the day into three levels: low-intensity, moderate-intensity, or high-intensity activities.

### Data management

Data will be collected by assessors using print-based case report forms (p-CRFs). And an identification code will be allocated for each participant to preserve anonymity. During the enrolment phase, two data managers will type the CRF into the computer and check the paper and the electronic data. All study co-applicants and researchers will have access to the final trial dataset. Plans that promote participant retention and complete follow-up are as follows: first, we will strengthen the communication between researchers and participants; second, we will give the participants some “financial incentive”; and third, all treatments and assessments will be free.

### Sample size estimation

Data from our pilot study was utilized to perform the sample size estimation. We used G-Power Software (version 3.1.9.2): F-test, ANOVA: repeated measures with the following parameters: effect size = 0.3; *α* level = 0.05; power (1 − β) = 0.80; group numbers = 2, number of measurements = 3. The total sample size of this study should be a minimum of 62 participants in the two groups. With a 15% attrition rate considered, the sample size of 72 participants is necessary.

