## Background

According to the World Health Organization (WHO), 6.2 million individuals die of stroke every year, while about 5.4 million survive [1]. Studies have shown that 75% of stroke patients live with cognitive impairments [2]. Post-stroke cognitive impairment (PSCI) is one of the most common factors leading to lifelong disabilities after stroke, which significantly impacts the patients’ activities of daily living (ADL) and their quality of life (QOL) [3, 4]. Moreover, healthcare and caregiving costs are high, which poses an economic burden for the healthcare system and families [5].

The symptoms of PSCI mainly include decreased memory, short attention span, decreased executive function, and dyscalculia. Side effects and clinical limitations of pharmacological therapy have been reported [6–8]. Mainstream post-stroke rehabilitation is based on neuroplasticity theory, which believes that repetitive practice after stroke can facilitate new synapses in the brain, thereby improving brain function [9]. As a non-pharmacological approach, exercise therapy has become a feasible strategy to improve PSCI [10, 11]. However, limited motor functions and decreased endurance due to stroke could prevent a post-stroke patient from participating in exercise activities. Low- or moderate-intensity mind-body exercise addresses physical and mental functions, which would be appropriate for this population, especially the older adults. Previous studies have shown that mind-body exercise can potentially improve motor function, psychological function, and ADL of stroke patients [12, 13] . As one of the traditional Chinese exercises, Yijinjing is a moderate-intensity exercise therapy based on traditional Chinese medicine theory. The Yijinjing exercises emphasize the combination of symmetrical physical postures, meditative mind, and breathing techniques in a harmonious manner. The Yijinjing exercise consists of linear movements and requires isolated joint movements. With simplified patterns and directions, Yijinjing is easy to practice with few limitations. The pilot study has demonstrated that the Yijinjing exercise helped improve older people’s physical and psychological outcomes in the community. This study’s primary purpose is to conduct a randomized controlled trial to evaluate the Yijinjing exercise’s effects in improving the cognitive functions of PSCI patients.

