### Statistical analysis

Statistical analyses will be carried out using SPSS software version 24.0 (SPSS, Inc., Chicago, IL, USA) and Microsoft Excel 2016 software. Data will be presented as means, standard deviations, and percentage changes. The intention to treat (ITT) principle will be used for statistical analysis, and the multiple imputation will reduce the missing data. Repeated measures ANCOVA will be applied for each measure to compare test performance between the Yijinjing exercise and routine treatment, with baseline scores used as covariates. Statistical significance will be considered at *p* value < 0.05.

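### The stated 80% power belongs to a three-measurement ANOVA that counts baseline as an outcome, not to the planned analysis with baseline as a covariate

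*Protocol article*

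**What the plan says.** All references are to the protocol article.

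- **Sample size estimation.** The calculation was run in G*Power as "F-test, ANOVA: repeated measures with the following parameters": "effect size = 0.3", alpha 0.05, power 0.80, and "group numbers = 2, number of measurements = 3". The result is that "The total sample size of this study should be a minimum of 62 participants in the two groups", raised to 72 for 15% attrition. The section names neither the effect tested (between groups, within, or interaction) nor the correlation among measurements.
- **Study design.** There are three assessments: one before the intervention, one at its end (week 12) and one three months later (week 24).
- **Statistical analysis.** Each measure is analysed by repeated measures ANCOVA, "with baseline scores used as covariates".

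**The concern.** The sizing and the analysis treat baseline differently. With three assessments in the schedule and three measurements in the calculation, baseline is counted as one of the outcomes. In the analysis it is a covariate and only weeks 12 and 24 are outcomes. These are different tests with different power.

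The difference matters because the test that reproduces 62 averages over all its measurements. At baseline the expected difference between randomised groups is zero, so including it dilutes any treatment effect. Adjusting for baseline instead removes variance. A power figure for the first test therefore says little about the second. The reader is left with 80% attached to an analysis that will not be done, and without the MoCA difference that 72 participants can detect.

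**Working it through.** **Inputs.** From Sample size estimation: f = 0.3, alpha 0.05, 2 groups, m = 3, N = 62, 15% attrition. From Study design: 1:1 allocation, one baseline and two follow-ups. Assumed, because the article gives no value: a common correlation rho between any two assessments, taken as 0.5 and varied, and equal SD at each visit. For two equal groups f = 0.3 is a difference of 2 × 0.3 = 0.6 SD. Power is from the noncentral F distribution.

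**1. Reproducing 62.** For the between-groups effect, lambda = N·f²·m / [1 + (m − 1)·rho], with 1 and N − 2 degrees of freedom. With rho = 0.5 and N = 62:

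lambda = 62 × 0.09 × 3 / 2 = 8.37, power 0.812.

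At N = 60 power is 0.799, so 62 is the smallest even total that reaches 80%.

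Other settings do not fit as well:

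| Setting (f = 0.3) | Total N for 80% power |
|---|---|
| Group-by-time interaction, m = 3, rho 0.5 | 20 |
| Group-by-time interaction, m = 3, rho 0 | 38 |
| MANOVA-type interaction, m = 3, rho 0.5 | 22 |
| Interaction, SPSS-type effect size | 58 |
| Interaction, Cohen-type effect size | 110 |
| Between groups, m = 2, rho 0.5 | 68 |

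The between-groups option with m = 2 would reach 62 at a correlation of about 0.35, but the article states three measurements. The between-groups option and rho = 0.5 are therefore an inference from an exact match.

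**2. What f = 0.3 means in that test.** If the groups differ by 0 at baseline and by D at both follow-ups, the three-visit average differs by 2D/3. Setting 2D/3 = 0.6 gives D = 0.9 SD. The sizing test thus has its stated power only if the effect is 0.9 SD at both follow-ups.

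**3. Power of the planned type of analysis.** Use 72 × 0.85 = 61.2, so N = 61, and d = 0.6 SD at both follow-ups. For the baseline-adjusted comparison, lambda = N·(d²/4) / v, with 1 and N − 3 degrees of freedom, where v is the residual variance:

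- Mean of weeks 12 and 24: v = (1 + rho)/2 − rho². At rho = 0.5, v = 0.75 − 0.25 = 0.50 and lambda = 61 × 0.09 / 0.50 = 10.98.
- Week 12 alone: v = 1 − rho². At rho = 0.5, v = 0.75 and lambda = 61 × 0.09 / 0.75 = 7.32.

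| Contrast (N = 61, 0.6 SD) | rho 0.2 | rho 0.3 | rho 0.5 | rho 0.7 | rho 0.8 |
|---|---|---|---|---|---|
| Mean of weeks 12 and 24 | 87% | 87% | 90% | 97% | 99% |
| Week 12 alone | 65% | 68% | 76% | 90% | 97% |

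**4. Difference detectable with 80% power, N = 61.**

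| Contrast | rho 0.3 | rho 0.5 | rho 0.7 |
|---|---|---|---|
| Mean of weeks 12 and 24 | 0.55 SD | 0.52 SD | 0.44 SD |
| Week 12 alone | 0.70 SD | 0.63 SD | 0.52 SD |

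**The case against.** The best defence has three parts.

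**The G*Power option and the correlation are back-solved.** The article states neither, and a condensed article may leave such settings to the full protocol. This stands as a limit on how firmly the source of 62 can be named. It does not remove the mismatch, which rests on stated text: three measurements in the sizing, three assessments of which one is baseline, and baseline as a covariate in the analysis.

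**The error does no harm.** The most natural reading of the planned analysis is a comparison over both follow-ups. For 0.6 SD at both, it has more than 80% power at every correlation examined. This largely stands and sets the severity. A reader might infer from the mismatch that the trial is underpowered, and the documents do not support that. Treating baseline as an outcome with 0.6 SD at both follow-ups would give about 47% for the three-visit average and 66% for group by time (N = 61, rho 0.5), but the article plans neither test. Power below 80% at week 12 alone depends on the correlation (76% at 0.5, 90% at 0.7) and on a contrast that the article does not single out.

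**A null result would still be readable.** This stands: it would be read from the estimate and its confidence interval, not from the planning power.

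Two further inferences are tempting and should not be drawn. One is that the attrition step undermines the sample size. Dividing 62 by 0.85 gives 73 rather than 72, a difference of one participant, and the sizing test still has power 0.806 at 61. The other is that f = 0.3 came from the wrong population. The Background mentions a pilot on "physical and psychological outcomes in the community" of older people, but the article does not say that this is the pilot used for the sizing, nor that MoCA was not measured in it.

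**Conclusion.** The concern holds as a sizing-versus-analysis mismatch of moderate severity. The arithmetic behind 62 reproduces, but it belongs to a test that includes baseline as an outcome, so the stated 80% is not the power of the baseline-adjusted analysis. For the same 0.6 SD, the planned type of analysis gives about 90% if both follow-ups are averaged and about 76% if week 12 is tested alone. The stated figure is thus roughly 10 points too low or 4 points too high, depending on a contrast that the sizing does not identify.

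These figures rest on a common correlation of 0.5, equal variances, the same effect at both follow-ups, and 61 participants' worth of information. The last is an approximation, since the plan is intention to treat with multiple imputation. The documents give no basis for calling 72 too few.

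**What to change.** Keep 72 participants. Rewrite the sample size paragraph for the baseline-adjusted MoCA comparison that will be tested, and state:

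- the contrast: week 12, week 24, or the average of the two;
- the assumed correlation between assessments, with a range;
- the target difference in MoCA points and in SD.

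Suitable wording would be: with 61 participants analysed and a correlation of 0.5, the trial has 80% power for 0.52 SD on the mean of the two follow-ups (0.55 to 0.44 SD for correlations 0.3 to 0.7). If week 12 alone is the contrast, the figure is 0.63 SD (0.70 to 0.52 SD). The sponsor must supply the MoCA SD to turn these into points, because the article does not give it.

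The cost is one rewritten paragraph and a changed power statement, which may move up or down with the contrast chosen. No participants or visits are added.

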### Statistical analysis

Statistical analyses will be carried out using SPSS software version 24.0 (SPSS, Inc., Chicago, IL, USA) and Microsoft Excel 2016 software. Data will be presented as means, standard deviations, and percentage changes. The intention to treat (ITT) principle will be used for statistical analysis, and the multiple imputation will reduce the missing data. Repeated measures ANCOVA will be applied for each measure to compare test performance between the Yijinjing exercise and routine treatment, with baseline scores used as covariates. Statistical significance will be considered at *p* value < 0.05.

### Safety and adverse events

If the patient has been randomized, adverse events (AE) monitoring will begin until the end of this study. Researchers will record any abnormalities on the CRF including dizziness, dyspnea, and fatigue and assess reported AEs for severity and relatedness to the intervention. All participants will also be instructed to report any other adverse effects to the researchers whenever they occur. Researchers will try their best to prevent possible AEs. In case of any discomfort during the participation, the participants will receive treatment and corresponding financial compensation. Serious AEs will be reported to the ethics committee, coordinating center, steering committee, and sponsor immediately.

### Organization

Members of the coordinating center include the director, information manager, database programmer, statistical analyst, project coordinator, and research assistants. Members of the steering committee include the study chair, data coordinating center director, statistician, and clinical center directors. In addition, the responsibilities of the endpoint adjudication committee are included in the ethics committee and the data management team is included in the coordinating center. Therefore, there is no independent endpoint adjudication committee and data management team.

### Dissemination

Results will be freely disseminated via a peer-reviewed report to the funder (Shanghai University of Traditional Chinese Medicine) and through open access journal articles and conference presentations. In addition, we will inform all participants of the results through a brief report. There will be no use of professional writers. Public or professional access to the full protocol, participant-level data and statistical code will be by request to the chief investigator.

## Discussion

As a traditional Chinese exercise, Yijinjing was developed based on the traditional Chinese Medicine theory and is related to harmonizing Yin and Yang, which connects the body with the mind to improve physical and cognitive functions. Most of the previous studies focus on the effects of traditional Chinese exercises on healthy older people. Therefore, this research is the first randomized controlled trial that evaluates the effectiveness of the Yijinjing practice for PSCI patients. We expect that Yijinjing will become an innovative and effective treatment approach to improve patients’ cognitive functions with PSCI and expect it to show superior effects compared with the control group. We also expect the study’s outcome to provide evidence for clinical workers and researchers working with post-stroke populations.

In the outcome measure stage, we will use multiple assessment tools to comprehensively evaluate the cognition domains ranging from global cognitive function to specific cognitive domains, such as memory, executive function, and visuospatial functions. However, this study still has some limitations. First, the insufficient sample size and short intervention time could be potential factors that affect the study outcomes. Next, treatment may likely be more successful involving interventions with individuals who have a robust home-support network. This research’s recruitment method may be more inclined to patients with strong family support, which will lead to a conclusion that may not apply to all stroke patients. Besides, this exercise may not be appropriate to the participants who have a low level of motor functions or no movement in the body’s affected side.

In summary, this study’s main objective is to investigate Yijinjing’s effectiveness in improving PSCI patients’ cognitive functions and explore the superior outcomes of Yijinjing compared with conventional rehabilitation therapy.

### Trial status

The study registration number is ChiCTR1900026532. The recruitment is in progress. Recruitment began on May 2019 and will be completed by May 2021.

